## Section IV: Research Plan

1. **Statement of Purpose:** What are the scientific aims of the study, or the hypotheses to be tested?

The aims of this study are:

1. To simulate and explore the feasibility of future implementation of a routine opt-out HIV testing protocol using rapid testing methods in the often-chaotic jail setting;
2. To determine the ability of subjects to pass a competency assessment in order to consent to routine HIV testing at varying times after entry into jail
3. To examine the acceptability among jail inmates of a routine HIV testing protocol using rapid HIV testing methods;
4. To evaluate the optimal time to perform routine HIV testing among inmates who are

competent to consent to testing, in a manner that not only maximizes public health but also attends to the safety and health status of individual inmates.

1. To assess the attitudes toward future widespread implementation of a routine rapid

HIV testing protocol by correctional, medical, and custodial staff

1. To assess the feasibility of implementing routine HIV testing in jails at different time points during and after entry processing from a systems operations perspective

Hypotheses:

1. A higher proportion of inmates approached for testing the night of intake will be

deemed incompetent to consent to testing (using the standardized MacArthur Competence Assessment Tool )compared to those inmates approached in the days after intake.

1. A higher proportion of inmates approached for testing the night of intake will present at

a higher risk for suicidal ideation and psychological distress (according to the nursing

staff’s mental health assessments and the standardized K6 psychological distress

scale) compared to those inmates approached in the days after intake.

1. A higher proportion of inmates approached for testing the night of intake will not

receive HIV testing (because they are either deemed incompetent or choose not to

provide consent for testing) compared to inmates approached on subsequent days.

1. A significant portion of individuals assigned to being approached for HIV testing on

Day 7 will leave the facility prior to Day 7 and will miss the opportunity to be tested.

1. Correctional medical and custodial staff will express resistance to implementing

widespread routine HIV testing in jail settings.

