None of the aforementioned studies adequately addresses the screening of inmates for psychological distress, intoxication, and withdrawal prior to conducting widespread HIV testing. A major challenge to implementing a routine HIV testing protocol in jails is determining the optimal time to test, taking into account an inmate’s ability to consent to testing and his or her level of psychological distress. Because the incarcerated experience high rates of suicidal behavior, mental illness, acute intoxication, and withdrawal, they might not be competent to consent to HIV testing or to receive a positive HIV test result, even though these same individuals might also be at highest risk for infection.1, 23 Therefore, when choosing the appropriate time to screen inmates for HIV, testing must be performed in a manner that not only maximizes public health, but also attends to the safety and health status of individual inmates. It is well documented that inmates are more likely to experience mental distress and present at a higher risk for committing suicide within the first 48 hours of incarceration.25, 26 A ten-year study of deaths in the Chicago Cook County jail found that suicides were the third leading cause of death among inmates, following heart and cerebrovascular disease.27 In addition, studies of jail populations at time of admission show that acute symptoms of serious mental illnesses requiring treatment are present in about 6% of males and 15% of females at booking.28, 29

Prisoners might be too distressed at their time of admission to consider the consequences of being HIV tested. In particular, distressed individuals might not be prepared to receive a positive HIV test result. Furthermore, recently incarcerated prisoners might be intoxicated or experiencing symptoms of withdrawal, thereby preventing them from providing informed consent. The challenge with postponing testing is that many individuals experience very short stays in jail, with about 1/3 leaving within 48 hours, followed by further attrition daily for the first week. Therefore, every day that testing is delayed a greater number of inmates will leave jail without being tested. Although several authors have acknowledged the importance of screening jail inmates for mental status and suicide risk before conducting widespread HIV testing, no literature exists evaluating the tradeoffs between early versus late testing with regard to individual health needs and public health benefit.

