Inmates who arrive on each intake night (Monday through Friday) will be assigned to be offered testing and approached for participation in the study at one of three time points based on the total number of inmates proceeding through intake that night and their arrival times to the jail. One third of inmates will be assigned to be approached for routine HIV testing and study participation the night of intake itself during routine health screening and mental health assessment (9pm – 1am). One third of inmates will be assigned to be approached for routine HIV testing and study participation the evening following intake when all arriving inmates undergo a routine physical exam. The final third of inmates will be assigned to be approached for routine HIV testing and study participation seven days after arriving at the facility. This last group will not have HIV testing conducted during any routine health procedures as with the first two groups. Even though there are no routine health procedures conducted at this time point, we are still interested in testing this group seven days after intake because many in this testing group would have received seven days of medications and have completed a detox protocol if necessary. We therefore believe that a higher proportion of individuals in this last testing group will be more stable and be competent to consent to testing compared to the prior testing groups, although many of them might have bonded out or been released from the facility by this point. Although this time point is of less interest than the first two time points, because this is a pilot study, we believe that the data we collect from testing at this time point would provide us with valuable information that could better inform our research design for conducting a larger testing study in the future.

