2. Delivery of all preliminary positive results will be given by HIV testing counselors working at both correctional facilities. Delivery of all negative results, however, will be delivered by research study staff. One of our main reasons for choosing this method is because we want to ensure that subjects diagnosed as preliminarily positive have sufficient time to meet with counselors for post-test counseling. Also, if counselors must meet with inmates to deliver both positive and negative results, they may not have enough time to deliver all results prior to new inmates needing to return to court or bonding out. This would mean that some individuals in the Day 0 testing group could bond out or be taken to court in the morning before receiving test results. The bondsman arrives at 8am at both facilities – therefore, in order to ensure that all subjects receive their test results before meeting with the bondsman, both positive and negative test results will be delivered early the following morning starting at 6:30AM.
3. Although delivery of negative test results by research study staff is not the current standard of care at both study sites, it does simulate the standard of care that would be delivered if routine HIV testing were to be adopted. According to the revised CDC guidelines for routine testing, “HIV-negative results may be conveyed without direct personal contact between the patient and the health-care provider.” Only HIV positive results should be communicated confidentially through personal contact by a clinician, nurse, mid-level practitioner, counselor, or other skilled staff. Furthermore, prevention counseling should not be required as a part of HIV screening programs in health-care settings. 2 This protocol of delivery of negative test results by research study staff has also been reviewed and preliminarily approved by the Department of Corrections Research Committee, pending a signature from the Deputy Commissioner. The DOC Research Committee must give final approval to any study proposed to be conducted in the Connecticut Department of Corrections.

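### No hypothesis counts inmates assigned to Day 1 who leave before that evening's offer, and the protocol does not settle whether time points are compared per inmate assigned or per inmate approached

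*Protocol*

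**What the plan says.** Section IV, Statement of Purpose, sets out two hypotheses on inmates who end up untested.

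- Hypothesis 3 names its first denominator at the start: "A higher proportion of inmates approached for testing the night of intake will not". The comparator, named at its end, is again people who were reached with an offer: "provide consent for testing) compared to inmates approached on subsequent days". So both sides of the comparison are inmates approached. The only reasons given for no test are incompetence and refusal.
- Hypothesis 4 starts from a different denominator, namely inmates assigned: "A significant portion of individuals assigned to being approached for HIV testing on". The day it then names is the last one alone, and its event is departure before the offer: "Day 7 will leave the facility prior to Day 7 and will miss the opportunity to be tested".

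Other places bear on release before Day 7.

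- Background describes short stays, "with about 1/3 leaving within 48 hours, followed by further attrition daily for the first week", and says that each further day of delay loses more inmates.
- 3.A.5.2, item 2, has the bondsman arriving at 8am. It explains the early delivery of results by the risk that "some individuals in the Day 0 testing group could bond out or be taken to court in the morning before receiving test results".
- The figure in 3.A.6 places the Day 1 offer at 5pm-9pm, after that same morning.
- 3.A.1 says of Day 7 that "this time point is of less interest than the first two time points", which makes Day 0 and Day 1 the comparison of most interest.
- 3.A.1 defines the primary outcome as a percentage of subjects who consent and are tested at a time point. 3.A.7 compares the proportion accepting in each group and cites release of as many as 50% within 72 hours as its reason. Neither says whether inmates released before their offer are in the denominator.

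**The concern.** Aim 4 asks for the best time to test, and Background frames this as a trade-off. Later testing finds inmates more stable, but some have already left. To judge Day 0 against Day 1, both sides of that trade-off must be counted. The hypotheses count the departure side only for Day 7, the arm the protocol calls less interesting. Followed as written, Hypothesis 3 compares Day 0 with later days among inmates still present, so a gain in uptake on Day 1 would not be set against the inmates lost overnight. 3.A.7 also says the data will supply the effect size for a larger randomized trial. An effect conditional on still being in the jail could therefore be carried into that design without being recognised as such.

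**Working it through.** **1. Table 1 as it stands.** With p1 at intake, p2 after intake, k = 2 post-intake subjects per intake subject, and p̄ = (p1 + k·p2)/(1 + k):

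n = [1.96·√((1 + 1/k)·p̄(1 − p̄)) + 0.8416·√(p1(1 − p1) + p2(1 − p2)/k)]² / (p2 − p1)²

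- Men, 60% v 76%: p̄ = 0.7067; n = (1.0929 + 0.4844)²/0.0256 = 97.2, rounded up to 98, as printed.
- Women, 75% v 88%: p̄ = 0.8367; n = (0.8874 + 0.4126)²/0.0169 = 100, as printed.

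All ten rows reproduce with two-sided alpha 0.05, 80% power, 2:1 and no continuity correction. The calculation has no term for release.

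**2. Time between the Day 0 and Day 1 offers.** 3.A.1 gives 9pm-1am for Day 0 and the 3.A.6 figure gives 5pm-9pm for Day 1. The gap runs from 16 h (1am to 5pm) to 24 h (9pm to 9pm).

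**3. Share gone before the Day 1 offer.** The protocol gives no such figure, so I interpolate from its two release figures. The shape of the curve is my assumption.

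| Anchor | Shape | Formula | 16 h | 24 h |
|---|---|---|---|---|
| 1/3 by 48 h | linear | t/144 | 11.1% | 16.7% |
| 1/3 by 48 h | constant rate | 1 − (2/3)^(t/48) | 12.6% | 18.4% |
| 50% by 72 h | linear | 0.5·t/72 | 11.1% | 16.7% |
| 50% by 72 h | constant rate | 1 − 0.5^(t/72) | 14.3% | 20.6% |

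The range is about 11-21%. If all of the 48-hour departures fell on the first morning, the loss would be 33.3%. That is a bound, not an estimate.

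**4. Tests per inmate assigned to Day 1.** Yield = uptake among those approached × (1 − loss). This reads 76% and 88% as uptake among those approached and applies them to Day 1 alone. Table 1 labels them only as subsequent time points, Day 1 and Day 7 collapsed, so both steps are assumptions.

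| Loss before offer | Men (Day 0: 60%) | Women (Day 0: 75%) |
|---|---|---|
| 0% | 76.0% (+16.0) | 88.0% (+13.0) |
| 11.1% | 67.6% (+7.6) | 78.2% (+3.2) |
| 20.6% | 60.3% (+0.3) | 69.8% (−5.2) |
| 33.3% (bound) | 50.7% (−9.3) | 58.7% (−16.3) |

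**5. Break-even loss.** Men: 1 − 60/76 = 21.1%. Women: 1 − 75/88 = 14.8%. The women's value lies inside the interpolated range. The men's lies just above its top.

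**The case against.** A hypothesis is a prediction, not a list of what will be counted. Hypothesis 4 predicts a large loss at Day 7 and does not say that Day 1 has none. A reader might infer that the plan drops Day 1 departures and so presents Day 1 as free of release loss. The documents do not support that. The primary outcome speaks of subjects at a time point. 3.A.7 ties its group comparison to release within 72 hours, a window that includes Day 1, and plans a regression on all intakes. Section VIII lists a correctional database with entry and release dates. An all-assigned analysis is therefore possible under this text. That objection stands: the denominator is left open, and these inmates are not excluded. It does not close the gap, because Hypothesis 3, the one place that names a population for the comparison, says approached.

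Aim 4 is worded around inmates competent to consent, and the sized comparison is intake against both later groups together, so a Day 0 v Day 1 ranking is not the primary inference. This also stands. However, Aim 4 invokes public health, and 3.A.1 ranks the first two time points highest.

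The size is soft. No Day 1 release figure is given, and 3.A.5.2 says only that inmates could bond out or go to court. A court trip is not shown to be a release. It would be wrong to conclude that Day 1 will do worse than Day 0, or that Table 1 is in error.

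The choice of analysis set could be left to an SAP. The populations named in the hypotheses are in the protocol, though, and the two hypotheses name different ones.

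**Conclusion.** The point holds as a gap in the hypotheses joined to an open denominator. Inmates assigned to Day 1 who leave before the offer fall under neither Hypothesis 3 nor Hypothesis 4, and nothing in 3.A.1 or 3.A.7 settles how they are counted. On the stated assumptions (interpolated release, Table 1 targets per inmate approached, applied to Day 1), the 16-point gain in men shrinks to between about 8 and 0 points per inmate assigned. The 13-point gain in women becomes about +3 to −5. Loss above 21.1% would reverse the ranking in both jails. The textual gap does not depend on these figures. They show that the expected loss is close enough to break-even for the choice of denominator to decide the answer to Aim 4. The sample sizes are not challenged. For a pilot this is an inexpensive improvement, not a fatal flaw.

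**What to change.** 1. Extend Hypothesis 4 to inmates assigned to Day 1 or Day 7 who leave before their offer, reported separately for each group and jail.
2. State in Hypothesis 3, the primary outcome (3.A.1, repeated in 3.A.4) and 3.A.7 that the comparison of time points for Aim 4 uses all inmates assigned to each time point as denominator. Inmates released before their offer count as not tested.
3. Report the rate per inmate approached alongside, since it answers the separate question of acceptability among those present.

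The cost is a few sentences and a count of pre-offer departures for about 100 more inmates per jail, from the kind of entry and release dates that Hypothesis 4 already needs for Day 7. These inmates will not have consented, Section VII requests no waiver, and Section VIII describes database use for subjects. The departures are therefore better obtained as counts by assigned group than as individual records. Hypothesis 4 already raises this issue for Day 7, and the change widens it. The post-intake advantage may also turn out smaller than Table 1 assumes.

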**3. Research Plan:** Please provide an orderly scientific description of the study design and research procedures as they

directly affect the subjects.

3.A Prospective Pilot Routine Opt-Out Rapid HIV Testing Study

3.A.1 Overview: This pilot study proposes to perform routine opt-out testing as part of intake for approximately three hundred individuals at each study site (see below for description of study sites). Currently, both of the facilities where this study will be conducted perform voluntary HIV testing upon request. We will work closely with HIV testing counselors, correctional officers, and medical personnel involved with intake procedures in order to simulate as closely as possible future implementation of a routine testing protocol based on current CDC recommendations, using rapid HIV testing methods .

Our primary outcome is the percentage of subjects who consent to and receive an HIV test at a given time-point at each facility. This primary outcome will be assessed independently for each the male and female jails, since the relevant policy question is within each gender rather than between them i.e., policy-making is largely made independently for male and female jails. Additionally, women and men may have different attitudes and feelings toward HIV testing in general, toward HIV testing in jail, and are likely to present with different rates of mental illness, substance withdrawal, etc. that could potentially affect the primary outcome.30, 31

Intake procedures are conducted for new arrivals at each facility every Monday through Friday. Those arrested or booked on Friday evening, Saturday, or Sunday must wait in their local court holding facility until the following Monday night when they arrive at York C.I. (females) or New Haven Community Correctional Center (males). In addition, physical exams are conducted for all new arrivals the evening after they arrive at the facility, during second shift (3pm-11pm), i.e. every Tuesday through Saturday.

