Structured Interviews: All interviews will be conducted during the second and third shifts in private settings. Questions will include information on demographics, history of previous HIV testing experiences, court dates, perceived likelihood of remaining incarcerated, willingness to HIV test now if it were made available, attitudes abut HIV testing in jails and prisons, symptoms of withdrawal, suicidal ideation, psychological distress, and an evaluation of medical ability to consent to testing using the MacArthur Competence Assessment Tool. The forms will be taken to taken to our data management office at the Yale University AIDS Program and entered into a relational database. Record storage conforms to HIPAA regulations. This information will then be used as part of our process measures to examine the frequencies of patients who are medically competent to opt out, their measures of psychological distress and various states of intoxication and withdrawal. This data will be analyzed to examine the time frame by which these outcomes change after the time of incarceration.

HIV Testing Results: Testing results will be recorded by study staff and taken to our data management office at the Yale University AIDS program for entry into an electronic database. Record storage conforms to HIPAA regulations. Research staff will also provide the counselors with the test results. Counselors will arrange for test results to be recorded in Department of Corrections’ medical records. Counselors will refer preliminarily positive subjects for confirmatory testing. All confirmatory positive test results will be reported to the Department of Public Health per state reporting guidelines. Inmates will be informed of these reporting procedures during the consenting process.

Correctional Databases: There is a correctional database that includes all information regarding dates of entry and release from the DOC, medical and psychiatric classification, and pending court cases. We will use this database to access demographic information about subjects for data collection and analysis.

- 1. What methods and procedures will be used to safeguard the confidentiality of subjects and their data?

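### Day 0, 1 and 7 run from jail arrival, but weekend arrestees arrive after about 21 to 75 hours in custody, so results cannot be read as time since incarceration

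*Protocol*

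**What the plan says.** The protocol uses two clocks.

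- **Clock of the groups: jail arrival.** Sections 3.A.1 and 3.A.5.1 say: "Inmates who arrive on each intake night (Monday through Friday) will be assigned to be offered testing" at one of three time points. Each night is split into thirds: the night of arrival (from 9pm), the following evening, and "seven days after arriving at the facility". Aim 2 uses the same clock, asking about competence "at varying times after entry into jail".
- **Clock of the rationale: incarceration.** Section IV.2 (Background) argues that "inmates are more likely to experience mental distress and present at a higher risk for committing suicide within the first 48 hours of incarceration". Section VIII (Confidentiality, Data Sources) plans to use the interview data "to examine the time frame by which these outcomes change after the time of incarceration".

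For part of the population the two clocks differ by days. Section 3.A.1 says: "Those arrested or booked on Friday evening, Saturday, or Sunday must wait in their local court holding facility until the following Monday night". They then enter the study jail as Monday-night intakes.

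The analytic plan (3.A.7) compares the groups with Mantel-Haenszel tests and names no stratum. Arrest date is not in the interview schedule under 3.A.5.1, nor among the items named for the correctional database in Section VIII.

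**The concern.** The case against testing on intake night rests on people being acutely distressed or unfit to consent soon after they lose their liberty. If Day 0 includes people already held for one to three days, it does not measure that state uniformly. Two uses of the data are then at risk:

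- A time course described as change since incarceration would rest on a clock that is wrong, by a varying amount, for weekend arrestees.
- A result pooled over intake nights could hide a difference between Monday and the other nights, and this would bear on Aim 4 (the optimal time to test).

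The background section criticises an earlier jail study for not reporting time after incarceration. As planned, this study would have the same gap for weekend arrestees.

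**Working it through.** **1. Prior custody at Day 0.** Inputs: weekend hold (3.A.1) and the 9pm start of intake-night testing (3.A.1). Assumption: evening starts at 6pm.

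- Earliest weekend arrest: Friday 6pm to Monday 9pm = 75 hours.
- Latest weekend arrest: Sunday midnight to Monday 9pm = 21 hours.

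Inmates seen later in the shift have been held a few hours longer.

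**2. Do the group labels order people by time in custody?** Day 1 contact is from 5pm to 9pm (figure in 3.A.6).

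- Arrested Saturday, seen Monday 9pm as Day 0: at least 45 hours (from Saturday midnight).
- Arrested Tuesday, taken in that night, seen Wednesday by 9pm as Day 1: at most 45 hours (from the start of Tuesday).

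So some Day 0 inmates are further from arrest than some Day 1 inmates.

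**3. How many might be affected?** The documents do not say. Assuming arrests are even over the week:

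- Weekend-held: Friday 6pm to Sunday midnight = 54 of 168 hours = 32%.
- Held 48 hours or more at Monday 9pm: Friday 6pm to Saturday 9pm = 27 of 168 hours = 16%.
- If half of the weekend-held are freed before Monday: 16.1/(16.1 + 67.9) = 19% weekend-held, and 8.0/84 = 9.6% at 48 hours or more.

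**4. Does this touch the sample size?** Table 1 was reproduced first. Formula (pooled-variance chi-square, k = 2 post-intake per intake subject, two-sided 0.05, 80% power):

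n = [1.96·√((1 + 1/k)·p̄(1 − p̄)) + 0.842·√(p1(1 − p1) + p2(1 − p2)/k)]² / (p2 − p1)², with p̄ = (p1 + 2·p2)/3.

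- Men, 60% v 76%: 98 per arm, as stated.
- Women, 75% v 88%: 100 per arm, as stated.

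The other rows also match, so the table is internally sound.

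Next, let w be the weekend-held share of Day 0 and f the fraction of the intake to post-intake gap they have already closed. The Day 0 rate becomes p1 + w·f·(p2 − p1), with the post-intake rate held fixed. Power at 100 per arm:

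| f | w | Men | Women |
| --- | --- | --- | --- |
| 0 | any | 81% | 80% |
| 0.5 | 10% / 20% / 43% | 77% / 73% / 62% | 77% / 73% / 63% |
| 1 | 10% / 20% / 43% | 73% / 64% / 39% | 73% / 64% / 41% |

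Here 20% is one of five equal nights and 43% is 3/7, three days' arrests arriving together. Neither w nor f is in the documents. If weekend-held inmates were worse off, f would be negative and the difference would widen: for men with w = 20% and f = −0.5, 16 + 0.2 × 0.5 × 16 = 17.6 points. The table shows what would follow under assumption; it does not estimate a loss.

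**5. Could the gap be filled later?** Intake night probably could, because jail entry dates are in the correctional database. Time since arrest might not: arrest date is not a named item, and Section VIII has the sheet linking names to study numbers destroyed at the end. For incompetent inmates, Section VI keeps a count only. Unless that count is kept by night, the first hypothesis cannot be split afterwards.

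**The case against.** The strongest reply is that the study asks about time since jail entry, and an intake programme can offer a test only once the person has arrived. Monday arrivals are part of the real intake population, so the pooled Day 0 rate answers the operational question. This stands for the primary outcome and the first three hypotheses.

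Two stronger readings are tempting, and the documents support neither.

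- **That weekend arrestees arrive already stabilised, so the Day 0 contrast is diluted.** No care in court holding is described, and 3.A.1 ties stability to seven days of medication and completed detox. Untreated distress or withdrawal could ease, persist or worsen over a weekend. The 48-hour statement covers distress and suicide risk, not intoxication or withdrawal. One might assume a 15-point Day 0 excess that vanishes in all weekend-held inmates and so falls to 15 × 0.68 = 10.2 points. But that gives no excess to people still under 48 hours; with the 48-hour cut it is 15 × 0.84 = 12.6. Both the 15 points and the nil effect are assumed.
- **That the primary comparison is biased or underpowered.** Every intake night, Monday included, is to be split into thirds, so the hold alone creates no imbalance. (Assignment depends on arrival times, so balance within Monday is intended rather than guaranteed.) Section 3.A.4 draws its planning rates from experience in the same jail system, so they may already include weekend arrestees.

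It is also fair to say that the choice of a Mantel-Haenszel stratum can be left to a statistical analysis plan. The data item and the counts by night cannot, because they must be collected during the study.

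**Conclusion.** The concern holds as a limit on interpretation. Day 0 mixes inmates who have just been arrested with inmates held for about 21 to 75 hours, given the 6pm and 9pm assumptions. Results by group cannot therefore be reported as change since incarceration, as Section VIII intends, or compared with the 48-hour rationale in Section IV.2. The affected share is not documented; even arrests would put it at about 19% to 32% of intakes, depending on weekend releases. The direction and size of any effect on competence, distress or uptake are unknown. Not knowing the direction is itself a reason to show Monday separately. The remedy is cheap and should be adopted before enrolment.

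**What to change.** 1. Keep jail entry as time zero for the primary outcome and the first three hypotheses. Time since arrest is not assigned, so using it there would replace the planned group comparison with one driven by day of arrest.
2. Record arrest date for consenting participants, and use time since arrest only for the time-course analysis in Section VIII. State that this analysis covers competent participants, since no individual data are kept on the others.
3. Keep the numbers approached, found incompetent, refusing and tested by intake night within each group. Tallies fit the count-only rule in Section VI.
4. Stratify the Mantel-Haenszel comparisons in 3.A.7 by intake night (Monday v Tuesday to Friday), within each jail. Report the two strata descriptively beside the pooled result.

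**Cost.** One date field and a tally sheet; enrolment and the primary contrast are unchanged. Monday is only a proxy for weekend custody, because it presumably also receives people arrested that day. Monday estimates will be imprecise: with 20 to 32 of 100 Day 0 inmates and uptake of 60%, the 95% half-width is 1.96·√(0.24/20) = 21 points to 1.96·√(0.24/32) = 17 points. That cannot support a separate timing recommendation in this pilot.
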